### **Data analysis**

#### *Statistical analysis*

The Data Management Committee including a statistician outside of the research team will verify the statistical analysis and the Quality Assurance Process.

The baseline characteristics of the units, and respondents (patients, staff members) will be summarised using descriptive analysis (mean [standard deviation], median [interquartile ranges] or proportions) and compared between each intervention group, respectively.

The analysis will be carried out on an intent-to-treat (ITT) basis. Assumptions of normality of the residuals will be investigated. For the primary outcome, incidence of coercion methods used at the baseline (year 2015), year 2016 (at the beginning of 2017), and year 2017 (at the beginning of year 2018) will be calculated. Possible differences in patient characteristics between the intervention and the control group at baseline will be tested by Chi-Square or t-tests based on type of variables. This analysis will help to decide whether baseline characteristics of patients should be adjusted for in the model for the primary outcome comparison after intervention. The hierarchical (participant nested within ward) Poisson model will be used to estimate and test the relative risk of being coerced in the intervention and the control group, which takes into account the length of staying of patient's in hospitals. With the same principle, for secondary outcomes, a hierarchical linear model will be used for normally distributed variables such as patient satisfaction and team climate, a hierarchical logistic model for dichotomous outcomes such as any admission or any adverse event, and the Poisson model for hospitalisation stay lengths or time spent in a seclusion room. A sensitivity analysis will be conducted by comparing the primary data at the follow-up and the fidelity information [47]. If poor fidelity was found for the primary data, we may consider evaluating change rate of coercive methods use between the two groups using all three measures over time by applying repeatedly measured models with random effects of hospital clusters. The results from the secondary analyses will be treated as exploratory. Estimates and confidence intervals will be reported only. The CONSORT guidelines for randomised trials [95] will be followed throughout our data analysis and the reporting of our study results. This study protocol follows the recommendations of the SPIRIT Statement [96].

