## Methods

### *Aim of the study*

To compare the effects of an educational intervention to usual practice (no specified staff education) on improving treatment culture and supporting team climate in staff members, which further could reduce the need for the use of coercive methods in psychiatric care. Although the intervention is designed to impact the daily practice and treatment culture of each hospital organisations, our attempt is also to improve outcomes at the level of the individual patient and nursing staff. Therefore, the outcomes of the study will be assessed from the organisational, patients', and staff members' points of view.

The primary objective is to investigate whether the educational intervention for staff will decrease the incidence of patient restrictions - specifically use of seclusion rooms on psychiatric wards of hospitals. The secondary objectives are to investigate whether the educational intervention changes the incidence of limb restraint, forced injection, physical restraint and service use in psychiatric hospitals. The study will also investigate whether the educational intervention for staff members changes patients' functional capacity, level of treatment satisfaction and quality of life. From the point of view of the nursing staff, the study will investigate whether the educational intervention effects team climate and staff turn-over.

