### Primary outcome

#### *Organisational outcomes*

The primary outcome of the study is the incidence of seclusion room use by patients in each unit. This will be assessed based on local (and national, if possible) health registers (Finnish Mental Health Act 1116/1990, [70]). The outcome will be measured at three time points: baseline (in 2015) based on local register (at the end of 2016), year 2016 (at the beginning of 2017), and year 2017 (at the beginning of year 2018). Information collected from each organisation is comparable across hospital organisations. The national register holder, Care Register for Health Care [71] gives instructions on how the information regarding treatment notifications shall be collected, recorded and sent annually to the National Institute of Health and Welfare. To ensure that the information about incidence of seclusions can be obtained in full detail, data will be collected either manually based on nurses' notes and/or medical registers at the local organisations.

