### Secondary outcomes

#### *Organisational outcomes*

Other types of coercive measures: incidence of other types of coercive measures used on patients (limb restraint, forced injection, physical restraint) according to the Finnish Mental Health Act (1116/1990, [70]) (yes/no), including the frequency and/or length (in minutes, if possible) of these measures. The outcome will be measured at three time points: baseline based on local register from year 2015 (at the end of 2016), year 2016 (at the beginning of 2017), and year 2017 (at the beginning of year 2018). Information to be collected in each organisation will be comparable based on the instructions of data recording by the National Institute of Health and Welfare. The data will be collected either manually based on nurses' notes and/or medical registers at the local organisations.

Service use (collected from local and/or national registers): type of admission, length of stay (days), death [yes]. The data will be collected either manually based on nurses' notes and/or medical registers at the local organisations. Information to be collected in each organisation is comparable based on the instructions of data recording by the National Institute of Health and Welfare [71]. The outcome will be measured at three time points: baseline based on local register from year 2015 (at the end of 2016), year 2016 (at the beginning of 2017), and year 2017 (at the beginning of year 2018).

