### **Power and sample size**

We have systematically searched for, but found no directly relevant past work [31, 91]. We assume that if the data will be obtained from local hospital registers by sampling 7 clusters (hospitals) with 265 subjects each in intervention group and 7 clusters with 265 subjects each in control group, we will have 80% power to detect a difference between the

## SUPPLEMENT 1

group proportions of -0.0400. The control group proportion is 0.1100. The intervention group proportion is assumed to be 0.1100 under the null hypothesis and 0.0700 under the alternative hypothesis. The test statistic used is the two-sided Z test (unpooled) with an overall significance level at 0.05. We may assume based on the hospital registers that sample size for the total population admitted in the study wards in one year will be 3710. However, if we consider a loss of 20% patients in the local care registers, [92] the total number of patients on the randomised wards should be about 4454 patients. (PASS 11 software [93]). Further, if we assume 50% response rate for patient survey [94] out of possible 3710 participants, we will assume that we will obtain 928 filled questionnaires during 6 month survey data collection period. The sample size calculation was adjusted for intra-cluster correlation at 0.005.

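### The primary outcome is seclusion room use, but the analysis section sets the primary test on coercion in general, so read literally it contains no confirmatory test of seclusion

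*Protocol*

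**What the plan says.** The outcome is fixed as seclusion in three places: the Methods part of the Abstract, the Aim of the study ("specifically use of seclusion rooms on psychiatric wards of hospitals"), and Primary outcome, Organisational outcomes: "The primary outcome of the study is the incidence of seclusion room use by patients in each unit".

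The remaining measures are secondary. Secondary outcomes, Organisational outcomes, lists "incidence of other types of coercive measures used on patients (limb restraint, forced injection, physical restraint").

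The Statistical analysis section uses different words for the primary analysis. It begins "For the primary outcome, incidence of coercion methods used at the baseline (year 2015), year 2016 (at the beginning of 2017"), and then says that a hierarchical "Poisson model will be used to estimate and test the relative risk of being coerced in the intervention and the control group", a model "which takes into account the length of staying of patient's in hospitals". If fidelity is poor, a fallback repeated-measures analysis is considered, again on the use of coercive methods. In this section seclusion is named only as time spent in a seclusion room, among the secondary outcomes. Secondary results are to be exploratory, with only estimates and confidence intervals reported.

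Power and sample size assumes "7 clusters (hospitals) with 265 subjects each in intervention group and 7 clusters with 265 subjects each in control group". It compares proportions with an unpooled two-sided Z test: "The intervention group proportion is assumed to be 0.1100 under the null hypothesis and 0.0700 under the alternative hypothesis". It does not say which event these proportions describe.

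**The concern.** The Protocol names a variable, a model and an effect measure for its primary test, and the variable is not the one it defined as the primary outcome. This is more than detail left to a later plan, because an analyst who followed the section as written would model the wrong event.

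Two errors become possible. A real fall in seclusion could be diluted by the other measures, or offset if they rose. Conversely, a fall confined to restraint or injection could be reported as success on the primary outcome. If the wording stays unresolved until results are known, either event could be presented as the planned one.

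**Working it through.** **1. What the term covers.** The Background reports 3,329 patients exposed to coercive methods in 2014 and divides them into secluded, limb-restrained, forcibly injected and physically restrained. The Abstract calls the last three other coercive methods, and the secondary outcomes section calls them other types of coercive measures. In each place seclusion is one member of the class. So in this Protocol's usage, being coerced is wider than being secluded.

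**2. The stated power reproduces.** Inputs from Power and sample size: 7 clusters of 265 per arm, intra-cluster correlation 0.005, 0.11 v 0.07, two-sided 0.05, unpooled Z.

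- Design effect = 1 + (265 − 1) × 0.005 = 2.32
- Effective n per arm = 7 × 265 / 2.32 = 1,855 / 2.32 = 799.6
- Power = Φ(0.04 / √[(0.11 × 0.89 + 0.07 × 0.93) / 799.6] − 1.96) = 0.800

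This is the power of a comparison of patient proportions. On the log relative-risk scale of a Poisson model, with equal exposure and the same design effect, the standard error is √[2.32 × (1/204.05 + 1/129.85)] = 0.171. Power is then Φ(0.452/0.171 − 1.96) = 0.75.

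**3. How far the two events differ.** Background counts, out of 25,552 inpatients:

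| Event | Patients | Share of inpatients | Share of coerced |
|---|---|---|---|
| Seclusion | 1,520 | 5.9% | 46% |
| Limb restraint | 696 | 2.7% | 21% |
| Forced injection | 787 | 3.1% | 24% |
| Physical restraint | 326 | 1.3% | 10% |
| Any | 3,329 | 13.0% | 100% |

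The four counts sum to exactly 3,329, so I treat them as non-overlapping. The any-coercion share is taken from the counts; the text prints 14%.

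**4. Dilution if only seclusion falls by the planned ratio, 0.07/0.11 = 0.636.**

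- Seclusion alone: ratio = 0.457 × 0.636 + 0.543 = 0.834, so 13.03% becomes 10.87%. Power by the formula in step 2 is 0.27.
- The Background places limb restraint in seclusion rooms. Counting those patients as seclusion room use gives a share of (1,520 + 696)/3,329 = 0.666. Ratio = 0.666 × 0.636 + 0.334 = 0.758, so 13.03% becomes 9.87%. Power is 0.51.

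**5. Why the event behind 0.11 needs a name.** The 0.11 equals neither 5.9% nor 13.0%. With the same ratio of 0.636 and the same clusters, power is about 52% for an event at 5.9% (5.95% v 3.79%) and about 87% for one at 13.0% (13.03% v 8.29%).

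**The case against.** The strongest reply is that the sentence opens by referring to the primary outcome, which the Protocol has already fixed as seclusion three times, so coercion may be loose drafting for the same thing. The section never says any coercion and defines no composite. That reading is possible. It does not remove the need for correction: the broad term is used for the calculated incidence, for the tested relative risk and again in the fallback analysis, and everywhere else it means the whole class.

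A reader might infer that the trial was powered on seclusion and is analysed on something else. The documents do not support this for the event, because the sample size section names none. The mismatch with what was powered is shown only for the scale: a difference in proportions against a relative risk that takes stay into account.

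A reader might also infer that adjusting for length of stay is an error, because stay is itself a secondary outcome. If stay entered as an offset, 10% longer stays with the same number of seclusions would give a ratio of 1/1.10 = 0.91. But the outcome is an incidence, for which a person-time rate is legitimate, and the section does not specify an offset. The proportion ever secluded is not neutral to stay either: with a constant daily hazard and 11% secluded, a 10% longer stay gives 1 − 0.89^1.1 = 12.0%, a ratio of 1.09 with no change in practice. The choice is a trade-off.

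Finally, the power figures in step 4 use national rates and assume no effect on the other measures, although the intervention aims at less coercive care in general. That objection stands, and they are illustrations.

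**Conclusion.** The Statistical analysis section is wrong as written. It names a broader event for the primary test than the one the Protocol defines, and literally followed it leaves seclusion without a confirmatory test. That any form of coercion is meant is an inference, but a sound one from the Protocol's own usage.

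The consequence cannot be sized exactly from the document. If only seclusion changed, by the planned ratio, power would fall from the stated 80% to about 27% or about 51%, depending on whether limb restraint in seclusion rooms counts as seclusion room use. Both figures rest on the 2014 national counts, on non-overlapping categories and on unchanged use of the other measures. The conclusion itself rests on the text and not on these figures.

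The difference of scale between the power calculation and the model is a lesser matter (about 75% against 80% for 0.11 v 0.07 with equal exposure). It calls for a stated choice of unit and does not require dropping the length-of-stay adjustment.

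**What to change.** - In Statistical analysis, replace the wording about coercion methods and being coerced with seclusion room use for the primary analysis. Make the same change in the fallback analysis. Keep limb restraint, forced injection and physical restraint as secondary.
- State one unit and effect measure for the primary outcome: patients secluded, or seclusions per patient-day. Either is defensible. The one not chosen can be a sensitivity analysis. Say whether limb restraint applied in a seclusion room counts as seclusion room use.
- In Power and sample size, name the event behind 0.11 and 0.07.
- Align the primary outcome, sample size and analysis sections on these choices.

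The cost is a few sentences and no extra data, since all the measures are already to be collected. If the event behind 0.11 proves not to be seclusion, or a per-day rate is chosen, the power statement must be recalculated. The change should be made before outcome data are compared by arm.

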### Study procedure

#### *Recruitment and randomisation*

Written information letter describing the study are to be sent to the administrators of each hospital organisation. They are given up to four week-time to show their preliminary interest and willingness to participate. This allows an adequate time for them to think through their decision and ask any questions related to the study.

Hospital organisations, within which there will be eligible wards, agreeing to participate will be randomly allocated to either receive staff education intervention (intervention group) or not receive staff education (passive control group). This allocation is organised by the research group as soon as baseline information of the wards is collected. The unit of randomisation is the hospital organisation within which there will be psychiatric wards. The cluster design will be used to avoid contamination in intervention effects between individual staff members. We will use centralised randomisation at the University of Turku (Department of Mathematics and Statistics) stratified by number of patient beds and nursing staff to assure as similar number of participants as possible in the intervention group as in the passive control group. Randomisation will be fully concealed and computer-generated by an independent statistician, who is not involved in the study. Investigators enrolling wards will not be able to foresee the assignment.

Data analysts will be kept blinded to allocation. Due to the type of intervention, allocation will be unmasked after randomisation to patients and their relatives, contact persons on each ward, health care staff delivering patient care on the wards, and the researchers participating in the intervention design and implementation; this will reflect real-world care. The Data Management Committee (DMC) will undertake ongoing safety surveillance. Investigators running the preliminary analysis for the DMC will be masked to data until investigators release the database. In addition, the statisticians and the National Register holder [71] responsible for Finnish routine data used in this study will be masked to ward allocation and patient data in each arm.

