**Measures****Background information**

Patients: The demographic information of the patients (age, gender, marital status, educational level, housing, employment status, number of psychiatric hospital treatment periods, the time of first contact with psychiatric services) will be collected as part of a patient follow-up survey.

## SUPPLEMENT 1

Demographics of unit of randomisation: The following information about the units will be described: a number of hospital beds, a number of patients, bed/patient ratio, a number of treatment periods, an average length of stay, gender ratio, patient average age, three most common diagnose (ICD-10) [76], and a number of staff/professional group. In addition, a short description of the ward type and treatment methods will be asked.

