### Declarations

#### *Ethics approval and consent to participate*

The preparation phase of the trial (focus group interviews with staff members, and patients and relatives in associations) has been approved by the Ethics Committee of the University of Turku (33/2015). The proposal related to national register data has been assessed by the Ethics Committee of the University of Turku (code 41/2015). The trial has been approved by the Ethics Committee of the Hospital District of Southwest Finland (ETMK:9/1801/2016) and permissions to conduct the pilot study and realise the study in psychiatric hospitals have been granted by the study organisations in 2016. The study has been registered with ClinicalTrials.gov (NCT02724748 [99]).

Interviews with staff members, patient groups and relatives will be done on a voluntary basis and written informed consent will be obtained. The unit staff/research team members will approach patients and their relatives to explain the purpose of the study and its arrangements both directly and in written format. Patients and their relatives will be given the opportunity to ask questions about the study. Those assessed as lacking the capacity to give informed consent, and those who decline to participate, will not be interviewed. Staff and patient surveys are voluntary and will not include names, social security numbers, or any other identifiable information.

Participants will be informed that they have the possibility to withdraw their consent, and they will be made aware that data collected before withdrawal may be used for research purposes. Participants will also be informed that refusal or withdrawal from the study will not affect their position as staff members, health care clients or have effect on their relative's care.

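### Baseline chi-square and t-tests with no stated allowance for clustering help choose the covariates of the primary model, which names neither the 2015 seclusion incidence nor the stratification factors

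*Protocol*

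**What the plan says.** All references are to the Protocol.

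- **Covariate choice (Statistical analysis).** "Possible differences in patient characteristics between the intervention and the control group at baseline will be tested by Chi-Square or t-tests", the test depending on the type of variable. The purpose follows: "This analysis will help to decide whether baseline characteristics of patients should be adjusted for in the model" for the primary outcome. No significance threshold is given and no allowance for clustering is mentioned.
- **Primary model (same section).** A hierarchical Poisson model with patients nested in wards, which takes length of stay into account. No covariate is named. The 2015 incidence is to be calculated. It enters a model only in a repeated-measures analysis that may be considered if fidelity turns out to be poor.
- **Randomisation (Recruitment and randomisation).** The unit is the hospital organisation, and allocation is "stratified by number of patient beds and nursing staff".
- **Baseline outcome (Primary outcome, Organisational outcomes).** "The outcome will be measured at three time points: baseline (in 2015) based on local register", then for 2016 and 2017.
- **Patient demographics (Background information).** These "will be collected as part of a patient follow-up survey". The ethics section adds: "Staff and patient surveys are voluntary and will not include names, social security numbers, or any other identifiable information".

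**The concern.** Three things are at issue.

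1. **The selection rule.** Under randomisation, a baseline difference between arms arises by chance. Its p-value says nothing about whether the variable predicts seclusion, which is what makes adjustment worthwhile. The tests named also treat patients as independent, although whole hospitals are allocated, so they react to ordinary between-hospital variation more often than their nominal level suggests. The form of the primary model then depends partly on the observed data.
2. **The variables.** The demographics that the Protocol lists for patients come from a follow-up survey. The patient survey measures start at the beginning of 2017, after randomisation in May 2016. With no identifiers, the answers cannot be joined to the register records that hold the primary outcome. It is therefore unclear which baseline patient characteristics the rule refers to.
3. **The better covariates.** The 2015 seclusion incidence is the obvious prognostic variable, and its collection is already planned. The Protocol brings it into a model only optionally, and only on a condition (poor fidelity) observed after randomisation. That is a second data-dependent choice. Neither stratification factor is named in the primary model.

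At stake are precision and the pre-specification of the primary analysis.

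**Working it through.** **Inputs from Power and sample size:** 7 hospitals of 265 patients per arm (1855 per arm), proportions 0.11 and 0.07, ICC 0.005, and a "two-sided Z test (unpooled) with an overall significance level at 0.05". The stated result is "we will have 80% power to detect a difference between the" arms of 0.04. The survey is expected to yield 928 questionnaires.

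**Assumed, not in the Protocol:** a 5% level for the baseline tests; an ICC of 0.005 for patient characteristics (the Protocol gives it for the seclusion calculation only); a correlation ρ of 0.5 to 0.9 between true hospital rates in 2015 and at follow-up.

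**Step 1: reproduce the stated power.**
- Design effect = 1 + (265 − 1) × 0.005 = 2.32.
- Variance sum = 0.11 × 0.89 + 0.07 × 0.93 = 0.163.
- SE = √(0.163 × 2.32 / 1855) = 0.01428, and 0.04 / 0.01428 = 2.802.
- Power = Φ(2.802 − 1.96) = 0.800. The 80% reproduces.
- With a t reference on 12 df (14 hospitals minus 2), the same inputs give 73.0%.

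**Step 2: how often an unclustered 5% test flags a chance difference.** Rate = 2 × [1 − Φ(1.96 / √design effect)].
- Register data, 265 per hospital: 1.96 / √2.32 = 1.287, so the rate is 19.8%. A beta-binomial simulation (20,000 runs, 7 v 7 hospitals, prevalence 0.3) also gave 19.8%.
- Survey data, 928 / 14 ≈ 66 per hospital: design effect = 1 + 65 × 0.005 = 1.325, and 1.96 / √1.325 = 1.703, so the rate is 8.9%.

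The two figures belong to different readings of which characteristics are tested. They should not be combined.

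**Step 3: power with the 2015 hospital rate as covariate.**
- Reliability of a hospital mean: R = 265 × 0.005 / 2.32 = 0.571.
- Correlation of observed hospital rates from two separate patient samples: r = ρ × R.
- The variance of the treatment comparison is multiplied by 1 − r².

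| ρ (assumed) | r | 1 − r² | Z test | t, 11 df | t, 9 df |
|---|---|---|---|---|---|
| no adjustment | – | 1 | 80.0% | 73.0% (12 df) | 73.0% (12 df) |
| 0.5 | 0.286 | 0.918 | 83.2% | 75.8% | 74.0% |
| 0.7 | 0.400 | 0.840 | 86.4% | 79.4% | 77.6% |
| 0.9 | 0.514 | 0.736 | 90.4% | 84.4% | 82.7% |

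The 11 df column charges one degree of freedom, for the 2015 rate alone. The 9 df column charges three, for the 2015 rate, beds and staffing, and assumes that the stratification factors explain no further variance. One stratum term with a single degree of freedom would fall between the two columns.

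**The case against.** **The covariates are not named rather than excluded.** The Protocol does not forbid the 2015 rate or the stratification factors, and a covariate list is often left to a SAP, which is not at hand. This stands as far as it goes: a reader might infer that these variables are ruled out, and the text does not support that. It does not rescue the selection rule, which the Protocol states itself, nor the placing of the 2015 data in a fallback that depends on fidelity.

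**The rule is soft and there are safeguards.** The tests only help to decide, there is no automatic threshold, data analysts are blinded to allocation, and the Data Management Committee, with a statistician from outside the research team, verifies the analysis. This also stands. Blinding limits steering towards a favourable result, but it does not make a baseline p-value a guide to prognostic value.

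**Bias is not shown.** A reader might infer that the primary result would be biased or its type I error inflated, or that chance imbalance in earlier seclusion practice is the main threat to the trial. The documents support neither. A flag leads at most to an extra covariate, and with few hospitals many flags would reflect real differences in case mix that happened to arise between the arms. No error rate for the primary comparison has been calculated.

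**The survey is not shown to be the only source.** The Protocol also lists gender ratio, average age and common diagnoses for each randomised unit, and says that local registers form the study database. The fair statement is that the variables meant are unclear, not that no usable ones exist.

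**The Z-test gains are optimistic.** They charge nothing for lost degrees of freedom. This is correct, and the t-reference columns are the more realistic guide for 14 hospitals.

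**Conclusion.** The point holds in a limited form. The Protocol fixes a poor way of choosing covariates for the primary model: tests that do not measure prognostic value and have no stated cluster adjustment, applied to characteristics it does not identify. Under the stated assumptions such tests would flag chance differences about 20% of the time on register data, or about 9% on survey data, against a nominal 5%.

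The 2015 seclusion incidence, the natural covariate, is given only a conditional and optional role. Pre-specifying it would add roughly 3 to 10 percentage points of power by the Z test, 3 to 11 with 11 df, and 1 to 10 with 9 df, at ICC 0.005 and a year-to-year correlation of 0.5 to 0.9. That correlation is undocumented, so only the range can be claimed. The case against the selection rule does not depend on the power gain.

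**What to change.** In Statistical analysis:

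- Delete the chi-square and t-tests as a step in choosing covariates, and report baseline characteristics descriptively.
- Pre-specify the primary model as follow-up seclusion adjusted for the 2015 seclusion rate of the hospital (or ward) and the stratification factors. Enter beds and nursing staff as one stratum term to save degrees of freedom.
- If patient-level covariates are wanted as well, name them in advance and confirm that they come from the registers and can be linked to the outcome.
- Make adjustment for the 2015 rate independent of the fidelity findings.

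The change is one of wording, since the 2015 incidence and the stratification variables are already part of the planned data. The statistical cost is one to three hospital-level degrees of freedom. If the year-to-year correlation is low this nearly cancels the gain: at 0.5 with 9 df, power goes only from 73.0% to 74.0%.
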